### Randomization

A balanced 1:1 block (size six) randomization stratified by center will be performed directly after surgery, using Research Manager (RM; version 4.5.0.1), a web-based computer program (Fig. 1). A research nurse who is not involved in the study generates the allocation sequence with RM. Intramedullary hip nail (IMHN), dynamic hip screw (DHS) and cannulated screws are grouped for block randomization, as are total hip arthroplasty (THA) and hemiarthroplasty (HA). The intervention group ‘A’ will receive CFC therapy postoperative; the control group ‘B’ will receive standard care. Due to the nature of the study no blinding can exist as patients, family and physicians notice the use and settings of CFC therapy. Physicians randomize participants with a digital logon to the web-based system or the physician can contact the coordinating investigator and he will randomize the included participant (see Table 1 for criteria).The Informant Questionnaire for the Cognitive Decline in the Elderly (IQ-CODE) questionnaire is administered when the clinician has doubts about the cognitive state that may compromise CFC therapy sessions or study measurements (Table 1). Ideally a MMSE would be used for this purpose, however due frequently perceived pain at the accident and emergency A&E department and consequently administered narcotic analgesics, the hetero anamnestic IQ-CODE is used instead. The coordinating investigator contacts the participating hospitals on a daily basis by telephone or physically to ensure adequate and appropriate enrollment of participants and completeness of data. A list of excluded patients will be drafted.

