## Statistics

### Analysis of outcome parameters

All statistical analyses will be computed using the SPSS statistical package (IMB SPSS, Inc., Release 20.0.0.0, 64-bit edition). Statistical analysis will be performed according to the intention-to-treat principle. Baseline characteristics will be described in accordance with CONSORT guidelines [41] using means and standard deviation in case of normal distribution, and medians and interquartile ranges otherwise. Continuous variables will be checked for normality, visually and by using the Shapiro Wilk test. Our primary analysis focuses on the differences in NRS-pain scores between the study groups 24 h postoperative and will be analyzed by use of Student’s T or Mann–Whitney U tests in case of skewed distribution. To assess treatment effect over time, a mixed model analysis for repeated measures will be performed. This model allows missing data and adjustment for serious confounders and interactions. In case of skewed distributions and outliers non-parametric variants will be used (e.g. Mann Whitney U or Friedman tests). Secondary continuous outcome measures (EQ-5D-3L, SF-12, DRS-R-98 and hemoglobin) will be compared by use of Student’s t or Mann Whitney U tests. Ordinal variables will be analyzed using the Mann–Whitney test. Chi-squared tests will be performed in case of categorical variables. In case of important confounding, analysis will be adjusted to correct for these factors (by use of multiple regression analysis, linear or logistic). A *p*-value of < 0.05 will be considered statistically significant.

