### Sample size calculation

Sample size calculation is based on the primary outcome measure, NRS-pain at 24 h postoperatively. Subsequently, a mean NRS-pain score for postoperative day one was drawn from the Spaarne Gasthuis electronic patient dossier digital databanks and a standard deviation of 2.2 was calculated for pooled internal fixation and (hemi) arthroplasty for cervical and peritrochanteric fractures. The minimal clinical relevant difference for NRS-pain is 1.3 out of 10 [53]. The alpha was set at 5 % with a power of 90 % due to anticipated heterogeneity in regard to operating techniques, general care protocols but predominantly in regard to pain protocols between the participating centers (Table 2). An expected NRS failure rate of 10 % is anticipated together with expected missing data a drop out of 22.3 % is computed. The total number of included patients will be 160.

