## Discussion

This multicenter study will evaluate the efficacy of intermittent application of continuous-flow cryocompression therapy administered in the first 72 postoperative hours after hip fracture surgery. Due to the multicenter design of the study the results can easily be translated to the general care of hip fracture patients. Conversely, some inequality in local hospital pain protocols is present but conversion through accepted algorithms [59, 60] make comparison feasible. Spinal anesthetized patients could have advantages over the general anesthesia group in the acute hours post-surgery in regard to pain scores and analgesic use since the effect of the latter ends immediately after surgery in contrast to the former that takes a few hours to wear off completely.

The varying types of fractures have different characteristics and demand a different surgical approach. Peritrochanteric fractures quite often have more extensive bony trauma and less soft-tissue trauma, and after surgical stabilization with a DHS or IMHN fracture micro-motion leads to prolonged and greater dynamic pain [6]. Conversely, in (hemi) arthroplasty the fracture-site is removed completely at the expense of increased (surgical-induced) soft-tissue trauma. Hence the efficacy of CFC therapy is likely to vary in patients with varying extent of soft-tissue trauma. Therefore stratification is implemented according to type of surgery that divides patients with greater surgical trauma ((hemi) arthroplasty) and lesser surgical trauma (cannulated screws, DHS, IMHN).

By nature, delirium is known to fluctuate over the day and a single DRS-R-98 measurement might not reach sufficient sensitivity for diagnosis. However with longitudinal follow-up of three times daily DOS-scores this problem is overcome for the most part. Delirium severity is assessed with more information gathered from family and personnel, over the past 24 h thereby making assessment adequate.

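### The primary 24 h pain comparison omits the randomisation strata and admission pain score, and leaves adjustment to an undefined condition; the test is valid but conservative.

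*Protocol article*

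**What the plan says.** Under Analysis of outcome parameters, the primary comparison of NRS-pain at 24 h between the groups "will be analyzed by use of Student’s T or Mann–Whitney U tests in case of skewed distribution". No covariate or stratification factor is attached to it. A mixed model for repeated measures is also planned, to describe the effect over time. It is said to accommodate missing values and adjustment for serious confounders. The general rule on covariates is "In case of important confounding, analysis will be adjusted to correct for these factors", by multiple linear or logistic regression.

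Under Randomization, "A balanced 1:1 block (size six) randomization stratified by center will be performed directly after surgery", with the fixation devices forming one group for blocking and total and hemiarthroplasty the other. The Discussion gives the reason, namely that efficacy may vary with soft-tissue damage: "Therefore stratification is implemented according to type of surgery that divides patients with greater surgical trauma".

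The Sample size calculation section expects the centres to differ, above all in their pain protocols. Table 4 and the Admission section show that NRS-pain is recorded at the emergency department.

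**The concern.** The protocol treats centre and type of surgery as important enough to balance on, then leaves both out of its main test. Stratified allocation removes most between-stratum variation from the treatment difference. An unadjusted test still counts that variation in its standard error, so the interval is too wide and some power is lost.

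The adjustment rule matters more for credibility. Neither important nor serious confounding is defined, and no covariates are named. Patients, staff and physicians all know the allocation, and the outcome is a verbal rating. A rule this open leaves room for adjusted and unadjusted results to be compared before one is put forward. In a randomised trial, baseline imbalance is due to chance, so prognostic covariates are best fixed beforehand.

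**Working it through.** **Inputs from the protocol.** "Sample size calculation is based on the primary outcome measure, NRS-pain at 24 h postoperatively". The difference: "The minimal clinical relevant difference for NRS-pain is 1.3 out of 10". The spread: "a standard deviation of 2.2 was calculated for pooled internal fixation and (hemi) arthroplasty". Alpha is 5% and power 90%; two-sided testing is assumed because it reproduces the stated size. Attrition: "An expected NRS failure rate of 10 % is anticipated together with expected missing data a drop out of 22.3 % is computed". Total 160.

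**Reproducing the sample size.**
- Normal approximation: n per arm = 2 × (1.96 + 1.282)² × 2.2² / 1.3² = 60.2, so 61. Total 122; 122 / 0.777 = 157.0, rounded up to an even 158.
- Exact t test: 61.2 per arm, so 62. Total 124; 124 / 0.777 = 159.6, so 160.

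The stated 160 reproduces. Power of the unadjusted t test with 62 per arm is 90.4%, taking 2.2 as the full SD and giving no credit for stratification.

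**Type I error of the unadjusted test.** Let R² be the share of outcome variance explained by the strata. The protocol gives no value, so 0, 0.1 and 0.2 are used. With perfect balance within strata:

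Type I error = 2 × [1 − Φ(1.96 / √(1 − R²))]

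- R² = 0.1: 3.9%
- R² = 0.2: 2.8%

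Balance will not be perfect, because the blocks are of six, the strata are small and scores will be missing. Simulation with 160 patients, ten strata (five sites by two surgery groups, an assumption), blocks of six and 22.3% missing at random gives about 4.2% and 3.5%. A repeat with 20,000 replicates gave 4.4% and 3.4%. These are the figures to use; the adjusted model stays close to 5%.

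**Power at a difference of 1.3, same simulation, strata terms only.**

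| R² of strata | Unadjusted | Adjusted |
|---|---|---|
| 0.1 | about 91% | about 92-93% |
| 0.2 | about 92% | about 95% |

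The gain is about 1-3 points. At R² = 0, a simulation that also fitted a baseline term gave 89.1% unadjusted and 88.0% adjusted. The repeat with strata terms only gave 90.1% and 89.7%. The cost is therefore half a point to one point.

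If admission NRS explained a further 10% of the variance, simulated power rose from 90.7% to 94.1% (strata 10%) and from 92.0% to 97.0% (strata 20%). The protocol gives no evidence on how prognostic that score is.

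**The open adjustment rule.** Taking whichever of the adjusted and unadjusted results is more favourable, after seeing both, gave a type I error of about 6-7% when the covariates were prognostic. A fixed rule (adjust only if the baseline imbalance has p < 0.10) gave 3.0-4.1% in the same scenarios. Any inflation comes from the lack of a rule, not from adjustment or from its omission.

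**The case against.** The strongest reply is that nothing here invalidates the trial. The test is conservative, the protocol sizes the trial for exactly this test, and it cites heterogeneity between centres as the reason for choosing 90% power. The SD comes from one hospital group's records, so it may contain little between-centre variance for centre terms to remove. A covariate list is also commonly left to an analysis plan. Most of this stands. It reduces the point to precision and pre-specification. It does not remove it, because the protocol itself fixes a primary test that cannot carry the strata.

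The reply on admission NRS also has force. Patients are given analgesics in the emergency department until their score falls below 4, and the protocol does not say whether the recorded score precedes or follows that. Its prognostic value is uncertain.

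A reader might infer several stronger things that the documents do not support:
- **That false positives are inflated.** Omitting the strata has the opposite effect.
- **That covariates will be picked after seeing results.** The wording permits this but does not say it.
- **That power falls to 82% if centre differences raise the SD to 2.5.** That figure treats centre variation as random error between arms. With total SD 2.5 and within-centre SD 2.2, stratified allocation leaves power at about Φ(1.3 / (2.2 × √(2/62)) − 1.96 × 2.5/2.2) = Φ(3.29 − 2.23), or about 85%.
- **That about 36 patients (22.3% of 160) are improperly discarded, many of them confused.** The 22.3% is an allowance already built into the sample size. The protocol does not say why these scores would be missing or whether such patients have other usable scores. How a missing 24 h score is handled may properly sit in the analysis plan.

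**Conclusion.** The point holds as a recommended improvement, not as an error of validity. The stated primary test ignores the factors used to randomise, and the adjustment rule is too loose to count as pre-specified.

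The efficiency loss is modest and rests on the assumed R² of 10-20% for the strata, ten strata, and scores missing at random. The larger benefit of changing the plan is that the covariate set is no longer open to choice. The sample size needs no change.

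**What to change.** Name as primary a linear model for the 24 h NRS, or the repeated-measures model already planned with its treatment contrast taken at 24 h. Include fixed effects for centre (the sites as used in randomisation), surgery group and admission NRS, and state which admission reading is meant. If the mixed model is chosen, it can also draw on other scores of patients who lack a 24 h value, where such scores exist. The missing-at-random assumption should then be stated.

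Replace the conditional sentence on confounding with this fixed covariate set. Keep the t or Mann-Whitney test as a sensitivity analysis, and use the same strata terms in the linear or logistic models for secondary outcomes.

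The cost is a change of wording, slightly more analysis work and a few degrees of freedom, worth up to about 1 point of power if the covariates turn out not to be prognostic. No additional data or patients are required.

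### The non-parametric fallback named after the mixed model (Mann-Whitney U or Friedman) cannot estimate the treatment effect over time, so it should not replace that model

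*Protocol article*

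**What the plan says.** All of this stands in the protocol article, Statistics, Analysis of outcome parameters, unless another section is named.

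- Distribution check: "Continuous variables will be checked for normality, visually and by using the Shapiro Wilk test". The text gives no cut-off and does not say how the visual and formal checks combine.
- Primary comparison, NRS pain at 24 h: Student's t test, or Mann-Whitney U if the distribution is skewed.
- Repeated measures: "To assess treatment effect over time, a mixed model analysis for repeated measures will be performed". The next sentence justifies this model by its tolerance of missing data and its scope for adjustment and interactions.
- Fallback, in the sentence after that: "In case of skewed distributions and outliers non-parametric variants will be used (e.g. Mann Whitney U or Friedman tests").

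Under Sample size calculation, the relevant difference is a difference on the NRS scale: "The minimal clinical relevant difference for NRS-pain is 1.3 out of 10". Under NRS-pain (primary), the outcome is an 11-point score from 0 to 10. It is to be compared before and after treatment within the intervention group, and between the two groups.

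**The concern.** From its position, the fallback reads as the replacement for the mixed model when scores are skewed or contain outliers. The question at that point is whether pain over time differs between cryocompression and control. Friedman ranks the occasions within each patient and asks whether occasions differ, and arm does not enter the test. Mann-Whitney does compare arms, but reduces each patient to a single value.

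The Aim section defines the aim as pain over the first 72 h, while the primary test looks only at 24 h. The mixed model is therefore the named analysis that covers the whole period. If it were replaced as written, the trial would lose the estimate of the arm difference over time and the three properties given as reasons for the model: use of incomplete data, adjustment and interactions.

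**Working it through.** **1. The plan's own figure.** Inputs from Sample size calculation: "The alpha was set at 5 % with a power of 90" %, difference 1.3, "a standard deviation of 2.2 was calculated for pooled internal fixation and (hemi) arthroplasty", and "a drop out of 22.3 % is computed". A two-sided test is assumed.

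Normal approximation: n per arm = 2 × (1.960 + 1.282)² × 2.2² / 1.3² = 2 × 10.507 × 4.84 / 1.69 = 60.2, rounded up to 61. The t-based calculation gives 61.2, so 62 per arm and 124 in total. Allowing for losses, 124 / (1 − 0.223) = 159.6, rounded up to 160. The stated total is reproduced, and 62 per arm is used below.

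**2. Can Friedman detect a difference between arms?** Adding a constant to every score of a patient leaves the ranks within that patient unchanged, apart from rounding and the ends of the scale. A constant treatment effect is therefore invisible to the test.

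Simulation: 124 patients, 4 occasions, mean 4, no time trend, between-patient SD 1.5, within-patient SD 1.6 (total √(2.25 + 2.56) = 2.19), scores rounded and limited to 0–10, 1,500 trials.

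| True arm difference | Friedman rejects | t test on patient means rejects |
|---|---|---|
| 0 | 6.2 % | 4.7 % |
| 1.3 | 4.6 % | 98.7 % |

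Friedman stays near its nominal 5 % in both rows. Running it separately in each arm gives two within-arm p-values and still no comparison of arms.

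**3. Missed occasions.** Friedman needs complete rows. The section on study apparatus and treatment schedule gives 10 to 12 treatments in 72 h, with control scores taken at the same times. No missing rate per occasion is stated. The 22.3 % is the sample-size allowance for the 24 h score and cannot be used as one. Assuming independent missingness, the share of patients with all 12 scores is 0.98¹² = 78 % at 2 % per occasion, 0.95¹² = 54 % at 5 %, and 0.90¹² = 28 % at 10 %. This is an illustration only.

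**4. How often would the switch occur?** The plan says that "a mean NRS-pain score for postoperative day one was drawn" but does not report the value, so means from 5 to 2.5 are assumed. Scores are drawn from a normal distribution with SD 2.2, rounded and limited to 0–10, 62 per arm, 3,000 trials per mean. Entries are the percentage of trials in which at least one arm gives p < 0.05.

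| Assumed mean | Shapiro-Wilk | Skewness test |
|---|---|---|
| 5 | 57 % | 2 % |
| 4 | 81 % | 5 % |
| 3.5 | 97 % | 11 % |
| 3 | 100 % | 23 % |
| 2.5 | 100 % | 45 % |

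A repeat run gave ranges of 58 % to 100 % and 2 % to 46 %. On both arms pooled, Shapiro-Wilk rejected in every setting, but the plan does not say that the arms are to be pooled for the check. Much of the Shapiro-Wilk rejection reflects whole-number scores and the bounded scale, neither of which is skew in itself.

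**5. Is the 24 h test harmed?** Here the scores were calibrated to an observed SD of 2.2, with 62 per arm, 4,000 trials per setting and a switch to Mann-Whitney if either arm failed Shapiro-Wilk. Type I error of the switching procedure was about 4.8 %. With a 1.3-point difference, power was about 0.90 for the t test and 0.89 to 0.93 for Mann-Whitney.

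**The case against.** The strongest defence is that Friedman is only an example, listed beside a test that does compare arms. The protocol plans within-group comparisons: NRS pain in the intervention group, DRS-R-98 scores and vital signs. Friedman may be meant for those. That reading is possible, but the sentence does not confine Friedman to it, and it follows directly on the mixed model and its justification.

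It can also be said that Mann-Whitney could be applied to the cumulated 72 h score defined under NRS-pain (primary). That would be a valid two-arm comparison of total pain. It would still give no course over time and no adjustment, and the sum is not comparable between patients once scores are missing.

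A reader might infer that the normality check will almost always force the switch. The documents do not support this. The stated trigger is skew and outliers, judged by eye as well as by Shapiro-Wilk, and no rule says that p < 0.05 decides. The mean and shape of the scores are not given. The exact threshold is a detail that a statistical analysis plan may supply, and its absence is not part of this point.

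A reader might also infer that the primary analysis is invalid. It is not: its only fallback is Mann-Whitney, which keeps type I error and power. What remains is that Mann-Whitney by itself gives no mean difference to set against 1.3 points, although nothing in the text prevents reporting one beside it.

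**Conclusion.** The point holds for the repeated-measures analysis. Neither test named as the fallback can deliver what the mixed model is planned for. Friedman's lack of an arm term follows from its construction, and the simulation only illustrates it: about 5 % rejection with or without a 1.3-point difference, where a simple comparison of patient means finds it in 98.7 % of trials.

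The probability of the switch is not established. It ranges from about 2 % to 100 %, depending on the mean and on whether skewness or Shapiro-Wilk decides. These figures rest on a rounded, bounded normal shape, and real scores may be more skewed.

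For the primary 24 h comparison the consequence is limited to how the effect is reported. The documents give no ground for replacing that comparison with another primary method.

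**What to change.** Three changes to Analysis of outcome parameters:

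1. Keep the mixed model as the repeated-measures analysis whatever the normality check shows. If its residuals are skewed, use robust or bootstrap confidence intervals.
2. Remove Friedman as a fallback for that model, or state that it serves within-group comparisons only.
3. Report the 24 h difference in means with a confidence interval, bootstrapped if needed, even where Mann-Whitney supplies the p-value, so that the result can be read against 1.3 points.

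The sample size stays at 160 and data collection is unchanged. The cost is a small change to the analysis text.

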**Table 4 Tab4:** Outcome assessment points

		Assessment point						
Item	Data collection instrument (unit)	Baseline (A&E department)	Day of surgery	24 h	48 h	72 h	Discharge	6 - 8 weeks (outpatient clinic visit)
Demographics	-	X						
Pre-fracture functional status	NMS, KATZ-ADL	X						X
Delirium risk assessment	DRAS	X						
Cognitive function	IQ-CODE	X						
	MMSE						X	X
Blood loss	Intraoperative loss *(cc’s)*		X					
	Drain output^a^ *(cc’s)*			X	X	X	X	
Outcome								
Pain	NRS	X	X	X	X	X	X	X
Analgesics	Acetaminophen	X				X	X	
	NSAID’s	X				X	X	
	Morphine	X				X	X	
Blood loss	Hemoglobin (mmol/l)	X		X		X		
Transfusion incidence	Number of units						X	X
Delirium	DOS-score	X	X	X	X	X	X	
	DRS-R-98^c^		X	X	X	X	X	
	Pyschotropic medication	X				X	X	
Length of stay^b^	*(Hours)*						X	
Functional outcome	TUGT						X	X
	DEMMI							X
	SPPB							X
	Rehabilitation location						X	X
	Rehabilitation duration						X	X
PROM	EQ-5D-3L							X
	SF-12							X
	Satisfaction questionnaire						X	
Complications	General						X	X
	Therapy related						X	X
Feasibility	Nurse staff questionnaire						At discharge of last patient	

*A&E* accident and emergency, *NMS* New Mobility Score, *IQCODE-N* Informant Questionnaire on the Cognitive Decline in Elderly patients, *MMSE* Mini Mental State Exam, *NRS* numeric rating scale, *PC* packed cells, *DOS* Delirium Observation Screening, *DRS-R-98* Delirium Rating Scale Revised 98, *TUGT* Timed Up and Go Test, *DEMMI* De Morton Mobility Index, *EQ-5D-3*
*L* EuroQol questionnaire, *SF-12* Short Form-12 questionnaire

^a^Including autologous reinfusion. ^b^Start count at admission and at the end of surgery. ^c^: administered when DOS ≥ 3

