### Admission

Patient demographic data are noted on admission as well as American Society of Anesthesiologists (ASA) class, current NRS-pain, delirium observation screening (DOS)-score, activities of daily living (ADL)-Katz score and the New Mobility Score (NMS; Table 4) [44–46]. Time of injury and arrival at the A&E department is noted. Patient delay intervals longer than 6 h are actively explored and reasons for delay are clarified e.g. if a patient was prone and unable to call emergency services.

A standard preoperative venous blood sample is taken in which hemoglobin, hematocrit and mean corpuscular volumes values are measured (Table 4). Upon admission the local hospital analgesic and antithrombotic protocol is started (Table 2). A geriatrician is consulted preoperatively in patients who are older than 70 years and will focus on: polypharmacy, risk reduction of falls, prevention and/or treatment of delirium, optimization of nutritional status. The ADL-Katz score and delirium risk assessment score (DRAS) [47] are completed upon admission; furthermore precipitating factors for delirium (bladder infection and/or retention, fixation, sleep deprivation, electrolyte abnormalities including renal function impairment) are noted throughout the hospital stay. After the operation the surgeon notes the intraoperative blood loss, the type of implant, if applicable intraoperative complications, randomizes the patient and determines the patient’s treatment schedule.

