### Outpatient visit

At the single outpatient study visit between six to eight weeks, the following parameters are assessed; current NRS-pain; analgesic use; mobility status by the TUGT, de Morton Mobility Index (DEMMI) and the Short Physical Performance Battery (SPPB); current living situation (rehabilitation or at home); wound status and complications (thrombosis, consolidation, infection, readmission). Furthermore the self-assessment health questionnaires EuroQol(EQ)-5D-3 L and Short Form (SF)-12 are completed. If not administered during admission the MMSE is completed (Table 4).

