### Functional outcome

#### Timed Up and Go Test

The TUGT is a functional mobility test that measures the time it takes a patient to get up out of a chair, walk 3 m and return in a sitting position. The test is easy to use and has sufficient clinometric characteristics [65], can predict short-term risk of new falls [66] and functional outcome over time [67]. Detailed instructions are provided to the patient: rise from the chair (knees at 90° flexion) when you hear “go”, walk at safe speed to the mark on the floor and back, the time stops when you hit the chair with your buttocks. The physical therapist will demonstrate how to perform the TUGT once. The average of three tests will be the final TUGT outcome and no trial run is performed. Postoperative mobilization policy is noted and patients are stratified in three groups: no weight bearing, partial weight bearing or full weight bearing. Preferably no walking aid will be used during the test but if needed, the patient can use any walking aid available, the type of aid used will be recorded. The updated NMS is administered at inclusion for data stratification purposes [44, 45, 68]. NMS will be classified as low when NMS is 2-6 and scored high when NMS is 7–9 [46].

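### EQ-5D-3L and SF-12 at 6–8 weeks are compared without covariates by default; prespecified adjustment for pre-fracture function, center and surgery group would replace an undefined trigger and gain precision

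*Protocol article*

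**What the plan says.** **Test.** Under Analysis of outcome parameters: "Secondary continuous outcome measures (EQ-5D-3L, SF-12, DRS-R-98 and hemoglobin) will be compared by use of" Student's t or Mann–Whitney U. DEMMI, SPPB and TUGT are not in that list and no test is assigned to them by name.

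**Adjustment.** The same section adds: "In case of important confounding, analysis will be adjusted to correct for these factors", by linear or logistic multiple regression. It names neither the covariates nor what makes confounding important.

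**Timing of the outcomes.** Under Outpatient visit: "Furthermore the self-assessment health questionnaires EuroQol(EQ)-5D-3 L and Short Form (SF)-12 are completed". Table 4 marks EQ-5D-3L, SF-12, DEMMI and SPPB at 6–8 weeks only, and TUGT at discharge and 6–8 weeks. None has a baseline.

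**Pre-fracture function.** The Admission section lists among the items noted at that point "activities of daily living (ADL)-Katz score and the New Mobility Score (NMS; Table 4". Table 4 carries both under "Pre-fracture functional status" with a baseline mark. A use for NMS is stated only in the Timed Up and Go Test section: "The updated NMS is administered at inclusion for data stratification purposes", followed by "NMS will be classified as low when NMS is 2-6 and scored high when NMS is 7–9".

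**Randomization.** It takes place directly after surgery and is stratified by center, with fixation procedures in one group and arthroplasties in the other. The Discussion calls this stratification by type of surgery.

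**The concern.** Pre-fracture mobility and independence plausibly explain part of the spread in health status and function 6–8 weeks after a hip fracture. With a two-sample test, that spread stays in the error term although the variables that could remove some of it are already recorded. Cutting NMS into two classes, where it is used at all, discards further information.

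The adjustment rule also depends on the data. In a randomized trial a baseline imbalance is a chance event. If the analyst decides after seeing it whether to adjust and for what, several results are available for each outcome and the protocol does not say which one will be reported.

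Two of the four candidate covariates, center and surgery group, are randomization factors. The Discussion expects efficacy to vary with the extent of soft-tissue trauma, and it warns that differences in geriatric care between hospitals may affect functional outcome. The default test carries neither factor.

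**Working it through.** **1. The plan's own figure.** The stated total is 160, for NRS-pain at 24 h, with SD 2.2, difference 1.3, alpha 5% (taken as two-sided) and power 90%.
- Normal approximation: 2 × (1.960 + 1.282)² × 2.2² / 1.3² = 60.2, so 61 per arm.
- t-based: 61.2, so 62 per arm and 124 in total.
- With 22.3% dropout: 124 / (1 − 0.223) = 159.6, so 160.

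The figure reproduces. It concerns the primary outcome, and nothing below changes it. No sample size is stated for the 6–8 week outcomes.

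**2. Are NMS and Katz-ADL valid covariates?** Both are noted on admission, and randomization follows the operation, so treatment cannot affect the admission values. The Table 4 row also has a mark at 6–8 weeks. Those later values come after treatment and must not be used as covariates.

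**3. Is the default tied to the absence of a baseline?** Hemoglobin has a preoperative value, which is subtracted under Postoperative blood loss and transfusion incidence, and it receives the same two tests. The choice of test therefore does not follow from the lack of a baseline.

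**4. Size of the gain.** Let r be the correlation between the covariates taken together and the outcome. In a linear model the residual variance is (1 − r²) times the unadjusted variance, and the effective number of patients is N / (1 − r²). The documents give no r, so a range is assumed. N = 124 is used for illustration (160 × 0.777 = 124.3); attrition at 6–8 weeks is not stated separately. The standardized difference is set to give 80% power unadjusted: (1.960 + 0.842) × √(2/62) = 0.503.

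| Assumed r | Variance factor 1 − r² | Interval width √(1 − r²) | Effective N (124 analyzed) | Power (80% unadjusted) |
|---|---|---|---|---|
| 0.2 | 0.96 | 0.98 | 129 | 82% |
| 0.3 | 0.91 | 0.95 | 136 | 84% |
| 0.4 | 0.84 | 0.92 | 148 | 86% |
| 0.5 | 0.75 | 0.87 | 165 | 90% |

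The formula ignores the small loss from estimating extra coefficients, which takes some of the gain at the low end of the range.

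**The case against.** The case against is substantial and narrows the point.

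- **No bias.** A two-sample comparison of randomized arms is valid without covariates. A reader might infer that the missing baseline for EQ-5D-3L and SF-12 distorts the comparison. It does not.
- **Adjustment is not excluded.** To say flatly that the outcomes are compared unadjusted would pass over the conditional regression clause and the planned use of NMS in the TUGT section. Unadjusted by default is as far as the text goes.
- **No stated reason.** A reader might infer that a simple test was chosen because there is no baseline. The protocol never says so, and hemoglobin contradicts it.
- **Function measures.** The sentence that assigns the tests does not name DEMMI, SPPB or TUGT, so it cannot be cited as fixing an unadjusted test for them.
- **Size.** The gain rests on an assumed correlation. At 0.2 it is at most 4% of the variance. The Conclusion describes patients as generally 70 or older and Table 1 excludes the most severe comorbidity, so pre-fracture function may vary less than an age limit of 18 suggests.
- **Place for the detail.** Covariate lists commonly belong in an analysis plan, which is not shown.

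All but the last stand as limits on the claim. The last stands in part. The absence of a covariate list alone would be no finding. But the protocol itself fixes the default test and makes adjustment depend on observed confounding, and a plan that prespecified covariates would depart from that wording. The protocol also commits to unconditional corrections elsewhere: hemoglobin for intraoperative blood loss, and length of stay for care given by family.

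**Conclusion.** The point holds as a minor one on secondary outcomes. The stated default for EQ-5D-3L and SF-12 is less precise than the collected data are likely to allow, and the rule for departing from it is undefined and depends on the data. The gain from prespecified adjustment is a variance reduction of 4% to 25%, equivalent to 129 to 165 patients where 124 are analyzed. This assumes a covariate–outcome correlation of 0.2 to 0.5, an approximately linear relation and admission values used as covariates. The documents can neither confirm nor narrow that range. The primary analysis and the total of 160 are unaffected, and the protocol contains no error of validity on this point.

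**What to change.** For EQ-5D-3L and SF-12, replace the confounding-triggered adjustment with a prespecified linear model on arm, admission NMS as a score rather than two classes, admission Katz-ADL, center and surgery group (fixation or arthroplasty). Assign the same model by name to DEMMI, SPPB and TUGT at 6–8 weeks. Report the adjusted estimate whatever the observed baseline balance. Since the protocol provides for skewed outcomes, keep a rank-based or transformed analysis as a sensitivity analysis, and say in advance which result is the main one.

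The cost is a change of analysis wording, made before the outcome data are examined. No visit, questionnaire or patient is added, and no baseline EQ-5D-3L or SF-12 in acutely injured patients is needed.
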